### 4.4.2 Resource use data

Data relevant to the use of NHS resources were collected in five routine questionnaires headed:

1. Healthcare Utilisation Form,
2. System Modification,
3. SAE Hospitalisation,
4. Medication, and
5. Follow up interview.

These were administered at baseline, 3, 6 and 12 months and then yearly with the final collection at trial exit.

Levels of resource use by patient will be estimated under the following seven headings:

1. System modification (including reasons from a pre specified list)
2. CVD medication by 11 classes at start of study and new medication during the study with date. Other medication was recorded as yes/no.
3. Cardiac tests/procedures as day case admission
4. SAEs resulting in a hospitalisation, divided between those related to the study and not, along with duration of hospital stay
5. Hospital admissions (any other HF related hospitalisations other than SAEs)
6. Use of GP and practice nurses and Cardiac / HF Specialist nurses
7. Outpatient appointments and any A&E attendances.

Of these, 1) to 4) are plausibly related to the intervention while 5) to 7) refer to wider changes in health service use. For each of these items, the cost will be estimated as number of contacts multiplied by unit cost. The unit costs for GPs, practice nurses and Cardiac / HF nurses will be taken from PSSRU^5^. Hospital services costs, including for SAEs will be taken from National Reference costs. Drug costs by class will be taken from the BNF and PPA. The unit cost of system modifications will be based on that of an outpatient or day case contact as recorded in the trial. The cost of any A&E attendances will also be included.

### 4.4.3 Medication Costs

The REM medication questionnaire collected data on 11 classes of CVD related drugs, by name. Mean cost per day for each of the more commonly used drugs will be estimated, with class means used for those used rarely or lacking full data. The prices will be combined with recommended daily dose to provide a medications cost per patient in each arm.

Clinical opinion suggests that efficacy was most likely to apply to changed use of diuretics. Aldosterone antagonists also matter due to their potential effect on mortality. The levels of use of each of these classes of drug will be shown separately. As AF was defined as a subgroup for analysis, the relevant drugs (warfarin, NOACs) will also be identified and costed separately. Cost units for all drugs will be calculated based on BNF.

System modifications (to the implanted device) would normally require an outpatient or day-case attendance. These will be identified by attendance type and costed as standard attendances.

Serious adverse events (SAEs) requiring hospitalisation are identified in the SAE questionnaire. The number of hospital days in each arm for SAEs and any other relevant conditions will be multiplied by mean NHS national HRG cost. This will be expressed as cost per day by dividing by mean length of stay^6-7^.

### 4.4.4 Cost Analysis

Costs will be estimated as the sum of the costs of the intervention, hospitalisations, and medication. They will be calculated by multiplying measures of resource use time estimates by unit costs for each type of resource^6-7^. The description of the services provided to the patients or the medical procedures used for the initiation of treatment or for use of the device will be provided by each centre.

The costing year will be the last study year prior to data unblinding (2014/2015) - if cost data are not available for this year, inflation of previous cost years data will be performed.

QALYs can be estimated from both EQ5D and SF12, both of which were administered at baseline, in addition to 12 and 24 months (or at trial exit if less than 24 months). The primary analysis will use EQ5D with the SF12 used in a sensitivity analysis.EQ5D will be used to estimate QALYs via the UK valuation set. Utility scores will then be multiplied by the duration of time spent in that health state and total QALYs will then be calculated with the area under the curve method.^8-12^

Both QALYs and intervention costs will be estimated at patient level once the final dataset is made available. This will enable both to be included in the statistical analyses described above. This will be done by the trial statistician or by the health economic team as appropriate.

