***Outcomes measured*:**

The primary endpoint will be combined all-cause mortality (ACM) or unplanned cardiovascular (CV) hospitalisation whichever came first.

The Endpoint Review Committee will adjudicate on :

1. the appropriate classification of cause of death, using data from primary and secondary care records, coroner reports and the death certificates. Mortality data will be obtained from the NHS Medical Research Information Service (MRIS)
2. underlying cause of hospitalisation using a standardised proforma and reviewing circumstances of hospitalisation from primary care records and hospital notes.

Secondary outcomes will include ACM, unplanned CV hospitalisation, CV mortality, unplanned CV hospitalisation, and unplanned hospitalisation.

*Quality of Life Assessment:* All participants will complete the SF-12, EuroQol (EQ5D), and Kansas Heart Failure Questionnaire (KHFQ) at enrolment, 3 months, 6 months, 12 months and 24 months. These will be administered by the study remote monitors. The initial quality of life forms will be completed at the time of patient enrolment in the hospital. Subsequent assessments will be performed by the patients in their homes. The forms will be sent to them by post with the necessary means for return of the forms. Receipt of the forms and their return will be managed by the remote monitors and local study administration staff. *Cost-effectiveness:* including cost of interventions, cost of Cardiovascular related health care.

Process measures will be collected to compare the pattern of care between the two arms and across centres (as we have no standardisation of usual care and the protocol is a pragmatic guideline and interpretation may differ between centres).

Key abnormalities detected in RM relate to atrial/ventricular arrhythmias and HF events. Key interventions are medication patterns, including anti-coagulation for atrial fibrillation.

There will be assessment of implementation of recommended interventions in the RM group and particularly those performed in primary care.

This flow chart summarises the study:

*- Acute care*

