## 2.4 Data Collection, storage and management

### 2.4.1 Data Collection

An electronic clinical report form (eCRF) was utilised to capture healthcare utilisation elements, QoL assessment and clinical events on a patient-by-patient basis. This should allow for an accurate and comprehensive assessment of the care pathway. All aspects of local data recording and management are the responsibility of the remote monitor lead in each site.

All participants will complete the SF-12, EQ5D-3L and KCCQ at enrolment, 3 months, 6 months, 12 months and 24 months. These tools were administered by the study remote monitor leads in each centre. The initial health-related quality of life forms were completed at the time of patient enrolment in the hospital. Subsequent assessments were performed by the patients in their homes. The forms were sent to them by post with the necessary means for return of the forms. Receipt of the forms and their return were managed by the remote monitors and local study administration staff.

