## 4.3 QoL assessment

EQ5D data will be used with the UK tariff to estimate differences in QALY increments. Values will be interpolated between collection points and differences estimated using area under the curve.

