### 4.3.2 Missing data

No imputation of missing data will be applied for the CEA data. Only patients with complete data will be included in the primary economic analysis, with imputation explored in sensitivity analyses.

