### 4.4.5 Incremental Cost-Effectiveness Analysis

The incremental differences in costs and effects will be compared between the intervention and control group and the incremental cost-effectiveness ratio (ICER) will be calculated using the formula: ICER = [costs (Intervention) – costs (control)] / [effects (intervention) – effects (control)].

Incremental costs and effects will be jointly bootstrapped and shown as a scatter plot on the cost effectiveness plane.

An ICER will be estimated for different levels of willingness to pay for a QALY using a cost effectiveness acceptability curve. Results will be compared with NICE’s threshold of £20,000 to £30,000.

The base case will be based on QALYs via EQ5D and NHS costs related to HF. Sensitivity analyses will include QALYs based on SF12 and on a range of monitoring costs based on different caseloads.

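### SAP 4.4.4 lists only the baseline, 12- and 24-month utilities for QALYs, although EQ-5D and SF-12 are also collected at 3 and 6 months; the ICER can depend on which schedule is used

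*Combined protocol and SAP*

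**What the plan says.** Three parts of the documents bear on which utilities enter the QALY.

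- **Collection.** SAP 2.4.1: "All participants will complete the SF-12, EQ5D-3L and KCCQ at enrolment, 3 months, 6 months, 12 months and 24 months". Protocol section 9 (Quality of Life Assessment) gives the same five time points for SF-12, EQ-5D and the "Kansas Heart Failure Questionnaire (KHFQ) at enrolment, 3 months, 6 months, 12 months and 24 months".
- **General method.** SAP 4.3: "Values will be interpolated between collection points and differences estimated using area under the curve". It names no visits and does not say what form of interpolation is meant.
- **QALY derivation.** SAP 4.4.4 says EQ-5D and SF-12 were "both of which were administered at baseline, in addition to 12 and 24 months (or at trial exit if less than 24 months", closing the bracket there. Months 3 and 6 are absent, and a trial-exit administration appears that 2.4.1 does not list. The section continues: "Utility scores will then be multiplied by the duration of time spent in that health state", and then "total QALYs will then be calculated with the area under the curve method".

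Two further rules depend on the answer. SAP 4.3.2: "Only patients with complete data will be included in the primary economic analysis", without saying complete at which visits. SAP 4.4.5 compares the result with the NICE "threshold of £20,000 to £30,000" per QALY.

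**The concern.** Incremental cost per QALY is secondary endpoint 19 in SAP 3.2.2, and cost-effectiveness is part of both the protocol's objectives and its hypothesis. The denominator of that ratio is an area under a utility curve, so the visits that define the curve are part of the estimator. One analyst could read 4.3 with 2.4.1 and use five visits. Another could follow 4.4.4 and use three. Each could claim to have followed the SAP.

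The first year is where this matters. On three visits the curve runs straight from baseline to month 12, so anything that happens in between is lost. The protocol gives a reason to expect something there. Its feasibility study (Background) reported better SF6D quality of life with remote monitoring at the end of a 6-month follow-up, and cautioned that the improvement might not last. That study was not randomised and proves no effect, but it makes an early gain that may fade a pattern the authors have already raised. Resource use is also collected at 3 and 6 months (SAP 4.4.2), so a three-visit QALY would rest on a coarser grid than the costs it is set against.

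**Working it through.** **1. Reproduce the plan's own cost-per-QALY arithmetic.** Appendix I, Table 3 follows from (nurse cost per patient + £100 × referral rate − share of admissions saved × inpatient cost) / gain.

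- 25% WTE nurse, 5% referred, none saved, gain 0.02: (150 + 5)/0.02 = £7,750, as printed.
- 100% WTE, 5% referred, 20% saved, gain 0.02: (600 + 5 − 0.2 × 771.25)/0.02 = 450.75/0.02 = £22,537.5; printed as 22,537.

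Table 2 prints the inpatient cost as £771. The value £771.25, which rounds to it, reproduces the 0% and 20% columns to within £1.

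**2. Area weights, in years.** Under the trapezoidal rule each visit is weighted by half the time to its neighbours.

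| Visit (months) | 0 | 3 | 6 | 12 | 24 |
| --- | --- | --- | --- | --- | --- |
| Five visits | 0.125 | 0.25 | 0.375 | 0.75 | 0.5 |
| Three visits | 0.5 | – | – | 1.0 | 0.5 |

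**3. Two-year QALY difference, as a multiple of the gain.** Baselines are taken as equal. The profiles are illustrative.

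| Between-arm gain | Five visits | Three visits |
| --- | --- | --- |
| Full from month 3, held to 24 | 0.25 + 0.375 + 0.75 + 0.5 = 1.875 | 1.0 + 0.5 = 1.5 |
| Full at 3 and 6, half at 12, none at 24 | 0.25 + 0.375 + 0.375 = 1.0 | 0.5 |
| Months 3 and 6 only | 0.625 | 0 |
| Linear to month 12, then held | 0.0625 + 0.1875 + 0.75 + 0.5 = 1.5 | 1.5 |
| Months 12 and 24 only | 0.75 + 0.5 = 1.25 | 1.5 |

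In the first row the three-visit area is 20% smaller, and the ICER is 1.875/1.5 = 1.25 times as large.

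**4. ICER for the first profile.** Gain 0.02, two years of cost, so ICER = 2 × annual cost / (multiple × 0.02).

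| Annual cost per patient | Five visits | Three visits |
| --- | --- | --- |
| £450.75 (the second Table 3 cell in step 1) | 901.5/0.0375 = £24,040 | 901.5/0.030 = £30,050 |
| £465 (Table 1, 0.75 WTE) | £24,800 | £31,000 |
| £310 (Table 1, 0.5 WTE) | £16,533 | £20,667 |
| £155 (Table 1, 0.25 WTE) | £8,267 | £10,333 |

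**5. How often this crosses a bound.** Multiplying each of the 36 cells of Table 3 by 2/1.875 (five visits) and by 2/1.5 (three visits), two cells cross £30,000 (printed as 22,537 and 23,287). Two others cross £20,000 (printed as 17,500 and, at a gain of 0.05, 16,000). The other 32 cross neither.

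**6. Complete cases.** Assume every baseline form is present and each postal form is returned independently with the same probability r. If all listed visits are required, the complete share is r⁴ on five visits and r² on three.

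| r | Five visits | Three visits |
| --- | --- | --- |
| 95% | 81% | 90% |
| 90% | 66% | 81% |
| 80% | 41% | 64% |

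**The case against.** The best defence is that the SAP, read as a whole, already points to five visits. Section 4.4.4 describes when forms were administered and nowhere says that the 3- and 6-month data are discarded. The operative rule in 4.3 interpolates between collection points, and 2.4.1 says what those points are. On this view 4.4.4 is an incomplete list. That is a fair reading and probably the intended one. It does not remove the problem: the section that specifies the calculation gives a schedule that contradicts the collection schedule, and no sentence says which visits enter the base case.

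A reader might also infer a second conflict, between a step function in 4.4.4 ("Utility scores will then be multiplied by the duration of time spent in that health state") and interpolation in 4.3. The documents do not support this. The same sentence in 4.4.4 ends with "total QALYs will then be calculated with the area under the curve method", so both sections name the same method, and the phrase about duration is loose wording for time-weighting. ICERs computed from a step function should carry no weight here.

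Nor does it follow that the choice of visits will decide the cost-effectiveness conclusion. The difference vanishes or reverses for some trajectories, and most Table 3 cells cross no bound. The £30,050 example passes £30,000 by only £50. The Appendix I inputs are 2003/4 scoping figures from a probably non-ICD population, and the appendix itself questions how representative they are.

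Finally, simply requiring all five visits would shrink the complete-case set (step 6). This objection stands, and the fix has to deal with it.

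**Conclusion.** The concern holds for the visit schedule. SAP 4.4.4 misstates when EQ-5D and SF-12 are collected, and taken literally it drops two collected utilities from the QALY area.

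For a gain present from month 3 and held, this understates the QALY difference by 20% and raises the ICER by 25%. An early gain that fades is understated more. A gain that builds linearly to month 12 is unaffected, and one that appears only from month 12 is overstated (1.5 against 1.25 times the gain). A crossing of £20,000 or £30,000 is therefore possible under the plan's own illustrative figures, but it is not the general case.

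These sizes assume equal baselines, no deaths, no discounting, straight-line interpolation, and illustrative costs and gains. The contradiction itself needs none of these assumptions. It should be corrected before the economic analysis so that the choice is not made after the data are seen.

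**What to change.** - **SAP 4.4.4.** State that base-case QALYs are the trapezoidal area under the utility curve through all available visits at 0, 3, 6, 12 and 24 months, and that the same rule applies to the SF-12 sensitivity analysis. Keep the trial-exit provision, which is the section's only rule for patients who leave before 24 months. Delete the phrase on multiplying by duration, or define it as the trapezoidal weighting.
- **SAP 4.3.2.** Define complete data for the QALY so that a missed 3- or 6-month form is bridged by interpolation between the adjacent visits and does not exclude the patient. Without this, naming five visits in 4.4.4 could cut the base-case set as in step 6 of the working.
- **Sensitivity analysis.** A 0/12/24-month area can be reported alongside, to show how far the result depends on the early visits.

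The cost is SAP wording and one optional extra analysis, since the 3- and 6-month forms are already in the collection schedule. The small downside is that patients with a missed intermediate form contribute a coarser area than the rest.

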### 4.4.5 Incremental Cost-Effectiveness Analysis

The incremental differences in costs and effects will be compared between the intervention and control group and the incremental cost-effectiveness ratio (ICER) will be calculated using the formula: ICER = [costs (Intervention) – costs (control)] / [effects (intervention) – effects (control)].

Incremental costs and effects will be jointly bootstrapped and shown as a scatter plot on the cost effectiveness plane.

An ICER will be estimated for different levels of willingness to pay for a QALY using a cost effectiveness acceptability curve. Results will be compared with NICE’s threshold of £20,000 to £30,000.

The base case will be based on QALYs via EQ5D and NHS costs related to HF. Sensitivity analyses will include QALYs based on SF12 and on a range of monitoring costs based on different caseloads.

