**Table 1**

**Illustrative cost of new service**

| Assumptions |  |  |  |  |  |
| --- | --- | --- | --- | --- | --- |
| Nurse | wte | 0.25 | 0.5 | 0.75 | 1 |
| Cost (gross £60k) |  | 15k | 30k | 45k | 60k |
| Patients | 100 |  |  |  |  |
| no requiring action |  | 5% | 10% | 15% | 20% |
| cost of action £100 |  | 500 | 1000 | 1500 | 2000 |
| Total service cost |  | 15.5k | 31k | 46.5k | 62k |
|  |  |  |  |  |  |

*Cost per QALY of new service*

The above analysis indicates that the new service may need to have large reductions on the need for inpatient admissions in order to be cost saving. However, the service could still be cost-effective even if not cost-saving. The descriptive statistics in appendix one indicate that he mean EQ5D score of those providing the cost data was 0.55. If we assume that the monitoring service and timely intervention could improve quality of life by either 0.02 or 0.05 we can estimate the likely cost per QALY of the new service (table 3). This is based on the QALY gain lasting for 1 year. Table 3 examines a number of different scenarios. These are: nurse service requires either 25% or 100% WTE, 0%, 20%, or 80% of inpatient admissions are saved and the nurse service refers between 5% and 200% of patients per year. It can be seen from table 3 that for a 0.02 QALY gain and a 25% WTE nurse service the cost per QALY appears to lie between £7,750 and £17,500 if no inpatient admission savings occur. These values are greatly reduced if 20% savings are assumed and under 80% savings the service would be cost saving. For the 0.02 QALY gain group all estimates lie between £40,000 and cost saving. If we assume a 0.05 QALY gain then all estimates like below £16,000 per QALY.

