### 1.2.2 Trial Outline

This is a randomised, multi-centre, open label (non-blinded), parallel group, clinical trial in which patients are randomised to receive either the control/usual care (UCP) or intervention (RCP) pathways on a 1:1 basis. The randomisation is stratified on both Site and Device type (ICD, CRT-D or CRT-P). Recruitment started in September 2011, and the target accrual is 1650 randomised patients (825 per group) but with an event driven design (see 2.3). Follow-up is for a minimum of two years.

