## 2.3 Study Power and Sample Size

Our sample size calculation is driven by a required number of events and uses event rate estimates from previous studies: this is an event-driven trial. The UCP group event rate is estimated from the COMPANION^2^ and CARE-HF^3^ trials, that both had a patient population that we expect to be comparable to our study control group. These trials reported 48% for any death or CV disease hospitalisation at 2 years, and 39% at 29 months for CV death or unplanned hospitalisation, respectively. We anticipate slightly lower rates in this trial due to an improvement in routine care, and so assume a 40% event rate for our primary endpoint of all-cause mortality or unplanned CV hospitalisation (see 3.2.1) in the control arm at 2 years.

The meta-analysis of Clark et al^4^ that looked at telemonitoring or structured telephone support, reported a 20% risk reduction compared to usual care. Hence we assume that the intervention group will have an event rate of 32% at two years. This reduction in event rate (from 40% to 32%) at two years, if seen, would be clinically relevant.

Fixing a 5% (2-sided) significance level and 90% power, 546 events are needed to detect this effect size in a log-rank survival comparison of the two trial groups. To achieve this number of events we are likely to require 1394 patients in total (697 per group) with a minimum follow-up of 2 years. We will inflate this total by approximately 20% to allow for attrition, giving a final recruitment figure of 1650. This sample size would also be sufficient to provide a reasonable estimate of the effect size in the individual components of the primary outcome – ACM and CV disease related unplanned hospitalisation. This sample size is considered feasible within the trial timescales.

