## 3.6 Secondary Analyses

Secondary clinical outcomes that are Time to Event will be analysed in a similar way to the primary endpoint. The analyses will be performed on adjudicated events in the ITT population. Subjects who are alive and event free at the end of the trial will be censored at the date of trial completion. Subjects who die (for a non-mortality endpoint) or who die for a different cause than the endpoint under investigation will be censored at their date of death. Those lost to follow-up will be censored at the date that their status was last known.

The total number of unplanned hospitalisations (for cardiovascular reasons and for all reasons) will be analysed using the Andersen-Gill model, a Cox regression model for counting processes. We will also explore the use of Poisson regression (with duration of follow-up included as an offset) and negative binomial models, depending on the range of counts that are seen in the data.

Continuous endpoints will be analysed using Analysis of Covariance (ANCOVA) including the baseline value as a covariate where available. Variables that appear to be skewed following a visual inspection of the separate group histograms will undergo a two parameter Box-Cox transformation prior to analysis.

Analysis approaches for the Health Economics endpoints are discussed in the Health Economics section (Section 4).

All secondary endpoint comparisons will be performed using the ITT population, and will include the same covariates as the model for the primary analysis (site and device type) and will be conducted using a 5% significance level. All estimates will be presented with 95% confidence intervals. There will be no imputation of missing values or adjustment of the significance level for multiplicity.

Time to event comparisons will be visualised using Kaplan-Meier curves.

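### SAP Section 4 specifies no baseline EQ-5D adjustment for the QALY difference behind the ICER, which leaves precision unused and the estimator open

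*Combined protocol and SAP*

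**What the plan says.** SAP 2.4.1 plans EQ-5D for all participants at enrolment and at 3, 6, 12 and 24 months. On QALYs, SAP 4.3 states: "Values will be interpolated between collection points and differences estimated using area under the curve". SAP 4.4.5 adds: "The incremental differences in costs and effects will be compared between the intervention and control group". It then gives the ICER as the intervention-minus-control difference in costs over the same difference in effects, with a joint bootstrap feeding the cost-effectiveness plane, and an acceptability curve. No covariate is named. The only sensitivity analyses listed there are SF-12-based QALYs and a range of monitoring costs.

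SAP 3.6 analyses continuous endpoints by ANCOVA with the baseline value where there is one, and applies site and device type to all secondary comparisons. Incremental cost per QALY is secondary endpoint 19 in 3.2.2. But 3.6 also says: "Analysis approaches for the Health Economics endpoints are discussed in the Health Economics section". Section 4 contains no regression model. SAP 4.4.4 closes by saying that patient-level QALYs and intervention costs can enter statistical analyses set out earlier, without saying which.

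The shells for Tables 7a and 7b in SAP 7.4 show the EQ-5D results adjusted for site, device type and baseline score. Table 8, for health economics, is listed in 6.1.2 but has no shell.

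**The concern.** The same EQ-5D scores serve two purposes. As change scores they are explicitly adjusted for baseline. As QALYs no adjustment is specified, although the baseline score is itself part of the QALY and is likely to predict the rest of it. Two analysts could follow this SAP in good faith and produce different ICERs, one adjusted and one not.

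Cost-effectiveness is part of the study hypothesis (protocol section 4, SAP 1.2.6). If the formula is applied as it stands, precision available from data already collected is given up, and a chance gap between arms at enrolment passes into the ICER.

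**Working it through.** **The plan's own figures.** The documents give no SD, precision or power for the QALY difference, so no stated figure can be reproduced for this point. Two nearby ones do reproduce:

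- The 546 events in SAP 2.3: HR = ln(0.68)/ln(0.60) = 0.755, which needs 533 events (Schoenfeld) or 540 (Freedman), both within 3%. This sets the sample size but says nothing about QALYs.
- Two Appendix I ratios: £15,500/100 patients = £155, and £155/0.02 = £7,750; £62,000/100 = £620, and £620/0.02 = £31,000.

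**Inputs from the documents.** 825 per arm (SAP 1.2.2); visits at 0, 3, 6, 12 and 24 months (2.4.1). SAP 4.4.4 names only baseline, 12 and 24 months, so both schedules are computed.

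**Assumptions.** Utility SD σ of 0.20 to 0.30, equal at every visit; the same correlation ρ, 0.4 to 0.7, between any two visits; no deaths; no missing forms.

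**Step 1: weights.** The trapezoid rule over two years gives weights w of 0.125, 0.25, 0.375, 0.75 and 0.5, summing to 2. The baseline score has direct weight 0.125.

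**Step 2: effect of a baseline gap.** A gap d shifts the expected raw QALY difference by b·d, where b = 0.125 + 1.875ρ.

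**Step 3: size of a chance gap.** SE of the baseline difference = σ√(2/825), which is 0.0098 at σ = 0.20 and 0.0148 at σ = 0.30.

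**Step 4: precision.** Var(QALY) = σ²[(1 − ρ)Σw² + 4ρ], with Σw² = 1.03125. The share explained by baseline is R² = b²/[(1 − ρ)Σw² + 4ρ]. Adjustment multiplies the SE by √(1 − R²).

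| ρ | b | R² | Cut in SE | Shift from one-SE gap (σ 0.20 to 0.30) |
|---|---|---|---|---|
| 0.4 | 0.875 | 0.35 | 19% | 0.0086 to 0.0129 |
| 0.5 | 1.062 | 0.45 | 26% | 0.0105 to 0.0157 |
| 0.6 | 1.250 | 0.56 | 33% | 0.0123 to 0.0185 |
| 0.7 | 1.438 | 0.66 | 42% | 0.0142 to 0.0212 |

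At σ = 0.25 and ρ = 0.6 the SE falls from 0.0206 to 0.0138. A simulation of 2,000 trials gave 0.0205 and 0.0138, with both estimators centred on the true difference.

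**Step 5: the shorter schedule.** With visits at 0, 12 and 24 months the weights are 0.5, 1 and 0.5, so b = 0.5 + 1.5ρ, or 1.10 to 1.55. The cut in SE is 28% to 49% and the one-SE shift 0.011 to 0.023.

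**Step 6: fewer patients.** The economic analysis uses complete data only (4.3.2). With 697 per arm, the figure in 2.3 before inflation for attrition, both SEs and the one-SE shift grow by √(825/697) = 1.09. The percentage cut does not depend on n.

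**Scale.** Appendix I supposes that the service could "improve quality of life by either 0.02 or 0.05", with the gain lasting one year. A shift of 0.009 to 0.021 QALYs is of the same order as the smaller value. As an illustration only, suppose that gain and the annual cost both run for two years (a further assumption): 0.04 QALYs and £1,240, or £31,000 per QALY. At ρ = 0.6 a baseline gap of 0.01 in either direction gives £1,240/0.0525 = about £23,600, or £1,240/0.0275 = about £45,100. The threshold range in 4.4.5 is £20,000 to £30,000.

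**The case against.** The strongest reply is that silence is not a decision. The ICER formula is the generic ratio and holds however each increment is estimated. Taken with 3.6, the cross-reference in 4.4.4 leaves a route to ANCOVA, and 3.6 read literally puts site and device type into every secondary comparison. This stands as far as it goes: a reader might infer that the SAP has chosen an unadjusted analysis, and no section says so. It does not show that adjustment is planned. Section 3.6 hands the methods to Section 4, its covariates for all comparisons exclude EQ-5D, and its ANCOVA rule uses an endpoint's own baseline value, which a QALY accrued over follow-up does not have.

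The second reply is that this concerns efficiency, not validity. That also stands. A reader might infer that the ICER is biased, but under randomisation the raw difference is unbiased on average. Chance imbalance is already part of the spread that the bootstrap and acceptability curve display, so the shift and the SE loss above are one problem seen from two sides. Baseline EQ-5D is tabulated by arm in Table 4a, so a gap would be visible.

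Third, the size rests on assumed values, and Appendix I is a scoping exercise with costs from a non-ICD population, not a design target. Agreed. A reader might also translate the SE loss into lost power, but 4.4.5 plans no significance test of QALYs, so power is the wrong measure.

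**Conclusion.** The point holds as a gap in specification with a clearly better method at hand. Section 4 specifies no baseline EQ-5D adjustment for the ICER denominator or its bootstrap, and 4.4.4 does not resolve the question. The documents do not support saying that the SAP declares an unadjusted analysis, or that the estimate would be biased by design.

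Under the assumptions listed, adjustment reduces the SE of the two-year QALY difference by about 19% to 42% on the five-visit schedule, and a one-SE baseline gap moves the raw difference by about 0.009 to 0.021 QALYs. Deaths add variation that baseline EQ-5D may predict less well, and correlations that fade with time would weaken the baseline score, so the true cut could be smaller. Complete-case selection could also add imbalance that is not due to chance; these figures do not cover that.

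**What to change.** In SAP 4.4.5, before the code break:

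- Define incremental effects as the treatment coefficient from a regression of patient-level QALYs on arm, baseline EQ-5D utility, site and device type.
- Define incremental costs as the treatment coefficient from a parallel regression on arm, site and device type.
- Refit both regressions within each joint bootstrap sample, keeping each patient's cost and QALY together.
- Use the resulting pairs for the ICER, the plane and the acceptability curve.
- Report the raw difference as a sensitivity analysis.

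The cost is a short paragraph and a few lines of code, since every variable is already collected. The primary economic analysis needs no baseline imputation: 4.3.2 already limits it to patients with complete data. A cost covariate for baseline resource use is not proposed. SAP 4.4.2 shows that the forms were administered at baseline, but not that they record prior use in a form suitable for adjustment.
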